#### Secondary Analyses

The key secondary analysis is the comparison of iCBIT to face-to-face CBIT in terms of YGTSS–TTS change 1-week posttreatment. If the primary objective of superiority of iCBIT over Placebo can be shown, this key secondary non-inferiority hypothesis can be tested in a confirmatory analysis with a one-sided significance level of 2.5%. The non-inferiority margin for the mean difference (iCBIT versus face-to-face CBIT) will be set to 3. The statistical analysis model is in line with the primary analysis described above (mixed model).

In further secondary analyses, the mean change from baseline to each time point will be tested in MRVS, ATQ, PUTS, GTS-QoL, WAI-SR, and the psychiatric comorbidity scores by means of an analysis of covariance between the treatment groups. The analyses will be adjusted for study site and concomitant tic medications as well as the baseline score of the respective outcome variable. Several subgroup analyses are planned as a function of pre-stratification-variables: comorbidities, age, gender, and duration of disorder. Further analyses investigating interactions terms will be conducted in order to assess the robustness of the treatment effect across the strata. Proportion of responders will be analyzed with logistic regression stratified in line with the primary analysis. All secondary endpoints will be analyzed in an intention-to-treat population.

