Therefore, the aim of this study will be to develop and test a fully self-sufficient Internet-delivered CBIT (iCBIT) for adult patients with TS, with no therapist involved in any way (ONLINE-TICS). Although interventions *via* video, Skype, or smartphone have been suggested (11, 17, 18) and, in addition, an RCT started only recently testing the efficacy of a computerized, self-administered version of CBIT (called http://TicHelper.com) in 64 children and adolescents with tics (age 8–18 years) (http://ClinicalTrials.gov Identifier: NCT02413216), to the best of our knowledge, so far, there is no iCBIT program available in any language for the treatment of tics in adult patients with TS and other chronic tic disorders. Since in TS – due to the natural waxing and waning course of tics – it is difficult to demonstrate efficacy of a treatment, only a well-designed and sufficiently powered study is suitable to demonstrate efficacy. Therefore, our study will be a multicenter, prospective, controlled, randomized, observer-blind clinical trial that aims to include 160 patients. ONLINE-TICS will be funded by the Federal Ministry of Education and Research (BMBF) in Germany (BMBF: 01KG1421). It is designed to examine the efficacy of an iCBIT intervention as compared to (1) a placebo platform consisting of psychoeducation only – which is our primary analysis – and (2) a conventional face-to-face CBIT intervention – which is our secondary analysis. We hypothesize that iCBIT (1) is superior to the placebo platform and (2) has a comparable effect size to the face-to-face treatment arm. Planned participating sites are Hannover Medical School (MHH), University of Munich, University of Aachen, University of Lübeck, and University of Dresden.

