### Sample Size Calculation

The sample size calculation is based on two studies in which the efficacy of face-to-face CBIT was compared with face-to-face psychoeducation in adult and pediatric patients with TS and chronic tic disorders (6, 7). The average YGTSS–TTS improvement across both studies was 3.5 (±5.5 SD), when comparing face-to-face CBIT to psychoeducation. The basic assumption of our study is that iCBIT is as effective as face-to-face CBIT. However, we expect a mean difference of 3.0 instead of 3.5 for the sample size estimation since only adult patients will be enrolled in this study, and a difference of three points is considered relevant enough to be detectable.

Under these conditions and with a one-sided type I error of 2.5%, *n* = 72 patients per treatment arm are required to reach a power of 90%. Therefore, a total of 144 patients will be included in the Internet-based treatment arms iCBIT and placebo. The expected drop-out rate is considered very low (<10%) based on previous studies in our centers and the studies by Wilhelm et al. (7) and Piacentini et al. (6). But even with as low as 60–65 patients per treatment arm a power of 84–86% can be achieved.

Sample size for the face-to-face CBIT arm in Hannover is feasibility driven. Sixteen patients will be randomized to face-to-face CBIT. The study is not powered for this secondary non-inferiority analysis.

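### The confirmatory non-inferiority margin of 3 points is as large as the planned gain over psychoeducation, so passing the test cannot by itself show that iCBIT is comparable to face-to-face CBIT

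*Protocol article*

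**What the plan says.** Under Data Analysis, Secondary Analyses, the comparison of iCBIT with face-to-face CBIT on YGTSS-TTS change one week after treatment is the key secondary analysis. It may be tested as confirmatory, at one-sided 2.5%, once iCBIT has been shown superior to placebo. The threshold is fixed there: "The non-inferiority margin for the mean difference (iCBIT versus face-to-face CBIT) will be set to 3".

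Under Sample Size Calculation, the historical effect is given as an average: "improvement across both studies was 3.5 (±5.5 SD), when comparing face-to-face CBIT to psychoeducation". For this trial, "we expect a mean difference of 3.0 instead of 3.5 for the sample size estimation", and "a difference of three points is considered relevant enough to be detectable". The same section adds: "The basic assumption of our study is that iCBIT is as effective as face-to-face CBIT". It also says that the face-to-face arm of 16 is driven by feasibility and that the non-inferiority analysis is not powered.

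The intended conclusion is that iCBIT "has a comparable effect size to the face-to-face treatment arm" (Introduction). The Abstract and Clinical Implications say much the same.

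**The concern.** A non-inferiority margin is the loss that the trial accepts while still claiming success. Here it equals the gain that the same article plans to detect and regards as relevant. A confidence interval reaching almost 3 points in favour of face-to-face CBIT would count as confirmed non-inferiority, yet it would leave open the loss of most of what face-to-face CBIT is expected to add over psychoeducation.

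At stake is the wording of a confirmatory claim. A pass would probably be reported as showing that an online programme without a therapist does as well as the established treatment, and the test as specified would not show that.

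**Working it through.** **Inputs.** Margin 3 (Secondary Analyses). Planning difference 3.0, historical difference 3.5, SD 5.5, 16 face-to-face patients, 72 iCBIT patients (Sample Size Calculation). The expected number of iCBIT patients in Hannover follows from Table 1 (62 patients) and Randomization (1:1:1 until 16 are in face-to-face CBIT, then 1:1): (62 − 16)/2 = 23. I use 23 and 72 as a range, because the article does not say how far iCBIT patients from the other sites inform this comparison.

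**The plan's own figure.** Difference 3.0, SD 5.5, one-sided 2.5%, power 90%: n = 2 × (1.960 + 1.282)² × 5.5² / 3² = 70.6, so 71 per arm by the normal approximation. The t-based calculation gives 72 (power 90.2%). The stated 72 is right.

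**Margin against effect.**
- Planning difference: 3/3.0 = 100%, so nothing need be retained.
- Historical face-to-face effect: 3/3.5 = 86%, so 0.5 points (14%) are retained.

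**What a pass requires.** SE = 5.5 × √(1/16 + 1/n). Writing the difference so that positive values favour face-to-face CBIT, the test passes if the observed difference is below 3 − t × SE.

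| iCBIT n | SE | t | t × SE | Largest observed difference that passes | 95% CI at that point |
|---|---|---|---|---|---|
| 72 | 1.52 | 1.988 | 3.02 | −0.02 | −3.04 to 3.00 |
| 23 | 1.79 | 2.026 | 3.63 | −0.63 | −4.26 to 3.00 |

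The hurdle for the point estimate is therefore high, but the interval after a bare pass still runs to 3 points worse.

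**Chance of passing at margin 3 (noncentral t), ignoring the superiority step.**
- True equality: 37% (23 vs 16) and 50% (72 vs 16).
- iCBIT truly 1.5 points worse: 13% and 16%.

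**Chance of passing both steps.** I simulated 72 vs 72 for superiority, then iCBIT vs 16 for non-inferiority, with SD 5.5 and a face-to-face effect over psychoeducation of 3.0 to 3.5.
- iCBIT truly 1.5 points worse: about 7–9% (23 vs 16) or 9–12% (72 vs 16).
- Truly 2.5 points worse: about 1–2%.
- Truly 3 points worse: below 1%.

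**A tighter margin, for illustration only.** At 1.75 (half of 3.5), the chance of passing at true equality is 16% (23 vs 16) to 21% (72 vs 16). An equally allocated trial would need about 156 per arm for 80% power or 208 for 90%.

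**The case against.** The best defence is the order of testing. Non-inferiority is examined only after iCBIT has beaten psychoeducation in the same trial, and that control matches iCBIT in number and duration of sessions. A reader might infer that an iCBIT no better than psychoeducation could be declared non-inferior. The documents do not support that, because the gate largely rules it out. It does not settle how much of the face-to-face benefit remains, which is what comparable asserts.

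A reader might also infer that so wide a margin makes the test easy to pass. With 16 face-to-face patients it does not: the point estimate must be near zero or favour iCBIT.

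The article nowhere calls a 3-point loss negligible, and its term is relevant enough to be detectable, not clinically relevant. The tension between the two uses of 3 points is real but is not a contradiction in words. Likewise, the 100% figure treats 3.0 as the adult effect of face-to-face CBIT, which follows only if the assumption of equal effectiveness is applied. The only effect stated for face-to-face CBIT is 3.5, which gives 86%.

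The statement that the analysis is not powered is candid, but it concerns sample size. It does not change what a pass would mean, and the test remains confirmatory. The lack of a written rationale for the margin is not held against a condensed article. The point rests on the number that is stated.

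**Conclusion.** The point holds in a limited form. A margin of 3 equals the planned gain over psychoeducation and is 86% of the historical face-to-face effect, so a pass cannot by itself support the claim of comparability. These ratios use only figures in the article and do not depend on the SD.

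The pass rates do depend on assumptions: SD 5.5, no dropout, simple two-group comparisons in place of the mixed model, and 23 to 72 iCBIT patients informing the contrast. Baseline adjustment could reduce the SD, and a pass could then occur with an observed difference somewhat in favour of face-to-face CBIT. Under the planning values, a misleading pass at a true 1.5-point loss has a chance of about 7% to 12%, and an inconclusive result is the likelier outcome.

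This is worth correcting, but it does not threaten the trial. The primary superiority test, its type I error and its sample size are untouched. The documents also do not support insisting on a margin of half the effect: that is a convention, and at these numbers it gives a test with little power.

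**What to change.** In Secondary Analyses, remove the confirmatory non-inferiority test at margin 3. Report the iCBIT minus face-to-face difference in YGTSS-TTS change one week after treatment, with its two-sided 95% confidence interval, as an estimate. State that 16 face-to-face patients cannot establish comparability, and bring the Abstract, Introduction and Clinical Implications into line.

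If a formal test is kept, give it a margin clearly below 3, tied to a stated share of the face-to-face effect that must be retained. State its low power, and fix it before unblinding, since a margin changed once results are known would not be credible.

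The cost is a change of wording and a lower chance of a non-inferiority claim, in an analysis already described as unpowered. No extra patients or data are needed.

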### Quality Assurance and Monitoring

To assure data quality and patients’ safety, regular monitoring visits will be carried out. An on-site initiation visit has to be performed, before a site is allowed to start recruitment. Periodic monitoring visits and source data verification will be done according to a risk-adapted approach (34). Close out visits will be done at the end of the trial and in case a site will be closed. Project managers and monitors will stay in close and regular contact with all trial sites.

Quality assurance will be realized by in-house monitoring *via* electronic data capture. On site source data verification will be done 100% for the first patient at each center and 20–50% reduced risk adapted monitoring afterward. In total, 16 periodic monitoring visits are planned (on average, two to three visits/site). If applicable, monitoring visits will be adapted according to recruitment.

### Safety

For this study, no safety issues have been identified. Adverse events and incidents will be documented *via* open questions and will be analyzed descriptively. Patients can contact the recruiting center at any time. If required, however, unblinding will be possible at any time.

## Discussion

### Clinical Implications

This is the first study examining the efficacy and safety of a fully self-sufficient Internet-delivered behavioral therapy using CBIT for adult patients with chronic tic disorders that does not require the supervision of a therapist (ONLINE-TICS). We will carry out a large multicenter, RCT in five different German TS centers to compare the efficacy of iCBIT [an online therapy, which follows closely the CBIT manual by Woods (20)] to (1) an online placebo – containing only psychoeducation – and to (2) a conventional and well-established face-to-face CBIT treatment. The inclusion of both an online-delivered placebo intervention and face-to-face CBIT gives us the unique possibility to investigate not only the superiority of iCBIT over placebo but also the non-inferiority compared to face-to-face CBIT.

We expect iCBIT to outperform the psychoeducation online platform (placebo) and to show a treatment effect comparable to face-to-face therapy. If shown to be effective, iCBIT will have several major advantages compared to face-to-face CBIT: (i) iCBIT can be delivered to any patient (the only requirement is a computer with Internet access), (ii) treatment of patients with TS according to latest guidelines will no longer be hampered by the lack of therapists trained in CBIT, (iii) iCBIT will shorten waiting time, (iv) iCBIT may be a treatment option even for those patients who refuse face-to-face psychotherapy due to reasons such as effort, costs, difficulties in reaching the therapist’s office (for example because of significant tics or a comorbid anxiety disorder), and personal career (since for example in Germany an appointment as a tenured German civil servant is no longer possible after a person has submitted an application for psychotherapy to his statutory health insurance), (v) costs for iCBIT will be much lower compared to costs for face-to-face CBIT, (vi) iCBIT guarantees highest quality standards, and (vii) there is evidence that Internet-delivered therapy in general reaches other groups of patients (e.g., homemakers, higher-educated people, employees, elderly people) as compared to regular face-to-face therapy (35). Therefore, we can assume that iCBIT will be an effective, safe, and cost-effective treatment for a substantial number of patients with TS. Thus, if effective, iCBIT will bridge a worldwide healthcare gap. In addition, one could think about combining elements of both types of treatment, face-to-face CBIT and iCBIT in order to improve efficacy (by giving the patient the possibility for timely flexible repetitions and the use of additional content such as videos, FAQ, and detailed psychoeducation) and flexibility (by using alternatively two different routes of delivery for CBIT) and as an aid for therapists in their work routine.

### Limitations

All of the treatment arms in our study compare behavioral interventions, but there is no comparison to medical treatment. Due to several reasons, we decided not to use a pharmacotherapy as an active comparator: (i) in Germany, only haloperidol is licensed for the treatment of tics, but it is no longer recommended due to significant adverse effects (5), (ii) due to lack of controlled clinical trials, the efficacy of those drugs most often used at least in Germany (tiapride, risperidone, and aripiprazole) is unknown (5) and, therefore, these drugs cannot be used as active comparators, (iii) until today there is no trial available comparing directly the efficacy of behavioral therapy versus pharmacotherapy, and (iv) using one of those drugs most often used for the treatment of tics would limit patient population, since a substantial number of patients would refuse participation.

Our study cannot be considered double-blind, since it will be very easy for patients to figure out if they are receiving iCBIT or not. This is a common problem that most studies examining psychotherapeutic interventions face. Nevertheless, our study has a high external validity. Treatment will not take place in a clinical setting, but in the homes of the participants. All treatment-related exercises will take place in patients’ everyday lives. There will be no issue with dissemination, since once shown to be effective, iCBIT can be made accessible to anybody seeking treatment for tics and will be delivered in the very same way, which was shown to be effective. We decided not to use a waiting list control designs, since it is well known that these trials may overestimate treatment effects. In order to make the control group more attractive, patients randomized to the control group will receive interesting and helpful information about their disorder in an entertaining presentation and, in addition, will have the possibility to receive iCBIT after study completion.

Our study examines an online treatment that works completely without the involvement of a therapist. Does that make therapists obsolete? Our answer is: definitely not. In our opinion, iCBIT offers a solution to overcome the lack of well-trained therapists. However, we do not intend to propose a program to replace consultation with a qualified medical doctor. An online treatment like ours cannot diagnose tics or test the indication for treatment; this always has to be done by a mental health specialist. Oftentimes, a patient might have several indications for treatment of which treatment for tics might be a minor one. This diagnostic work always has to be done by an expert. That being said, our platform will be a very useful tool to supplement therapeutic work in the private practice. The platform could assist the patient with regular homework and exercises, while a therapist could focus on helping the patient troubleshoot as well as work on other issues that the patient might have. This would be a timesaving combination for both the patient and the therapist.

### Conclusion

Our study ONLINE-TICS will test the efficacy of iCBIT – an online version of the highly effective face-to-face CBIT, which is the current first-line treatment for tic disorder. If shown to be effective, it will have the potential to bridge a large gap in the current health-care system in the treatment of tic disorders in Germany.

## Ethics and Dissemination

### Informed Consent and Institutional Review Boards

The study is based on the principles of Good Clinical Practice (GCP), according to the Declaration of Helsinki. Patients will be given oral and written explanation of the study including its potential risks, their right to withdraw consent at any time and the details of data protection and confidentiality and sufficient time to ask questions. A signed consent form will be obtained. The patient information and a copy of the signed consent form will be handed to the patient. The data will be monitored by HCTC. All documents and information will be treated with strict confidentiality.

Each study site will only be able to start data collection once the local Institutional Review Boards (IRB) approval is obtained. In the case of protocol changes an amendment will be submitted to the concerning IRB.

### Confidentiality

The information collected in the study, especially the information related to the identity of the patient, will be confidential and protected by law. The data collected at each study site will be stored and analyzed in de-identified form and kept for a period of 10 years in a lockable cabinet or password protected computer.

The collected data will be only accessible to the principal investigator and study staff of the respective study site as well as the monitors.

The Minddistrict company will not have access to any personal data of the study participants. The necessary login data will be provided and managed by the MHH research personal. Additionally, the Minddistrict portal will be SSL-encrypted.

Video recordings from all participating study sites will be saved on an encrypted cloud offered by the University of Goettingen.

### Dissemination

After study completion, the results of the primary and secondary analyses will be published in international peer-reviewed journals.

If shown to be effective the therapy platform will be made available to the general public in Germany in an appropriate manner. For this purpose, all necessary contractual arrangements between the MHH and the company Minddistrict will be clarified and defined before the beginning of the study. Currently, all rights to the Internet platform iCBIT belong to the MHH represented by [name].
